### Study procedure

#### Recruitment and randomisation

Firstly, subjects will be recruited by the sport research team. Information about the study, the neurostimulation technique, and the objectives of the research will be given to each subject by a trained psychiatry investigator. Enrolment date and timetable of visits will be scheduled directly with the volunteers.

After the informed consent is signed, a clinical exam will be conducted in order to verify the inclusion and exclusion criteria.

Subjects meeting the inclusion criteria will be randomised 1:1 into two (part A) or three (part B) groups using a minimisation technique with stratification according to their athletic level (hours of practice). Recruitment will be achieved when the number of subjects by groups is obtained.

After randomisation, a sequence of predefined codes will be generated by a computer. These predefined codes correspond to either the active or sham stimulation and will be used by the psychiatry staff to start the stimulator, allowing a double-blind study design. Each subject will present a control subject with the same randomisation sequence.

#### Blinding

Patients, researchers, and medical staff will be blind to the allocation to either active or sham stimulation. A computer-generated predefined code will be used to start the computer program connected by Wi-Fi to the stimulator. Correspondence between the codes and the type of stimulation will only be available after unblinding at the end of the study.

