To clarify the effect of tDCS on these different types of neuromuscular performance, we propose to evaluate the acute and repeated effects of tDCS during two tasks: an explosive task (jumps) and an endurance task (20-min cycling trial). The main objective is to compare the effects of tDCS applied over the left dlPFC with sham tDCS on the performance of the neuromuscular system. In the present protocol, the choice has been made to recruit participants with different backgrounds regarding sports practice, from sedentary people to high-level athletes in the targeted performance (parkour athletes for explosive performance or cyclists for endurance). Indeed, the tDCS effects on physical performance could also be a function of the initial level [23].

This study is a monocentre, sham-controlled, randomised, crossover, double-blinded superiority trial comparing active tDCS versus sham tDCS. It is divided into two parts: part A with the jumpers and part B with the cyclists. We hypothesise that the active tDCS sessions will improve motor performance and reduce neuromuscular fatigue. We will seek a better understanding of the factors that could cause tDCS effects to vary: stimulated brain area, exercise type (explosive vs enduring), tDCS configuration (cephalic vs extracephalic montage), and the number of tDCS sessions (single vs repeated stimulations).

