## Methods/design

### Study setting and overview

This research will be carried out through a collaboration between the Psychiatric Department of the University Hospital of Besançon and the scientists from the Faculty of Sports of the University of Besançon (C3S Laboratory). All experiments will take place on the EPSI research platform (Entraînement Performance Santé Innovation, Besançon, France). This protocol will be divided into two parts to explore the effects of tDCS by type of exercise:
Part A, which assesses the effects on explosive performance (jumps)Part B, which assesses the effects on endurance performance (cycling time trial)

Fifty subjects (20 in part A, 30 in part B) will be recruited from the university or from federated organisations of sports. For part A, athletes practicing parkour, an activity that consists of jumping obstacles in various environments, have been chosen since they usually present a very explosive neuromuscular profile [24]. For part B, amateur and professional cyclists will be recruited. After information about the study, written informed consent will be obtained.

In part A, subjects will be divided into two groups (amateur vs high-level practice) and receive three sessions of tDCS (active over the left dlPFC vs active over the right M1 vs sham over the left dlPFC). The session order will be randomised (Fig. 1).

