### Interventions

#### Transcranial direct current stimulation

Direct current will be delivered by a neurostimulator system (StarStim®, Neuroelectrics©, Barcelona, Spain) that allows a sham double-blind mode. It will be transmitted by two saline-soaked synthetic sponge electrodes (Sponstim®, 25cm^2^) placed in a neoprene head cap.

In part A, subjects will benefit from three 20-min sessions of tDCS (two active and one sham), separated by a minimum of 48 h. Electrodes will be placed according to the EEG 10–20 International System (Table 1) and sequence order will be determined by computer randomisation.

**Table 1 Tab1:** Electrode placement and stimulation parameters in part A

Part A	Sequence order determined by randomisation		
Anode	F3 over left dlPFC	FC_2_ over right motor cortex	Sham: F3 over left dlPFC
Cathode	AF8 over right supraorbital region	Controlateral shoulder	AF8 over right supraorbital region
Intensity of stimulation	2 milliAmpers	2 milliAmpers	0 milliAmper

In part B, subjects will benefit from two sequences of 20-min tDCS sessions per day, for 5 days consecutively (either a sequence of ten active or ten sham sessions according to the computer randomisation). After a wash-out of one month, they will receive the second sequence (crossover). The anodal electrode will be placed over F3 (left dlPFC) and cathodal electrode over AF8 (right supraorbital region). The intensity of stimulation will be 2 mA (in active sequence) or 0 mA (sham sequence).

For sham stimulation, in each part of the protocol, the current will gradually ramp up over 30 s until 2 mA at the beginning of the stimulation and will then gradually ramp down over an equal amount of time at the end, thus leading to the same initial and final sensations of active tDCS.

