## Discussion

COMPETE is an ambitious protocol that will seek to understand the acute and long-term effects of tDCS on physical performance. It will compare the tDCS effects on two types of exercise (explosive vs endurance) using a different administration mode (single vs repeated sessions).

The challenge of this study will be to specify the action mechanisms of tDCS on performance according to the exercise type, the stimulated brain area, the tDCS configuration type, and the level of athletes included.

To the best of our knowledge, this study will be the first to assess the effect of tDCS on different sport performance by gathering psychometric and neuromuscular measurements. It will determine whether and how the improvement or disruption of the cognitive dimensions studied (mood, motivation, and impulsivity) could affect explosive and/or endurance performance.

Finally, some authors have already argued that tDCS may be considered as a new form of doping. Many athletes use tDCS during training for several hours [41], although the effects of prolonged administration are unclear. Our study could determine if chronic use involves risks for them and raise the question of legislation around the free use of tDCS.

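### In part A the shoulder montage is only ever active, so the double-blind claim holds for dlPFC versus sham but not for M1, and area cannot be separated from montage

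*Protocol article*

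**What the plan says.** The Blinding section states: "Patients, researchers, and medical staff will be blind to the allocation to either active or sham stimulation". It rests this on computer-generated codes that start the stimulator, and it makes no exception for any condition.

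Study setting and overview lists the part A conditions as "active over the left dlPFC vs active over the right M1 vs sham over the left dlPFC". The intervention section gives each subject "three 20-min sessions of tDCS (two active and one sham"), and its Table 1 gives the layouts:

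- active dlPFC: anode F3, cathode AF8;
- active M1: anode "FC_2_ over right motor cortex", cathode "Controlateral shoulder";
- sham: anode "Sham: F3 over left dlPFC", cathode AF8.

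Part B uses F3/AF8 only, for both the active and the sham sequence.

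The Background names dlPFC versus sham as the main objective. It then lists factors to be better understood: "stimulated brain area, exercise type (explosive vs enduring), tDCS configuration (cephalic vs extracephalic montage), and the number of tDCS sessions (single vs repeated stimulations"). The Discussion says the challenge is to specify mechanisms "according to the exercise type, the stimulated brain area, the tDCS configuration type, and the level of athletes included".

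**The concern.** A stimulator code hides the current but not where the electrodes sit. If one layout is used only for active stimulation, the layout reveals the condition. The outcomes are maximal-effort jumps, and the long jump is repeated until the subject stops improving, so expectation and encouragement can influence the result. The analysis section plans a condition factor with three levels, and the Outcomes section compares active or sham sessions without restricting the active session to dlPFC. M1 results could therefore be presented as double-blind when they are not.

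The second issue is attribution. If brain area and montage never vary independently, a difference between M1 and dlPFC cannot be credited to either. The protocol's own Background shows why this matters: it cites a comparison in which the M1 anode was kept and the cathode moved between a cephalic and an extracephalic site, with different results. The same question arises for exercise type, which is compared across two parts that differ in several other ways.

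**Working it through.** **Blinding, by layout (part A)**

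| Session | Layout | Current |
|---|---|---|
| dlPFC active | F3/AF8 | active |
| Sham | F3/AF8 | sham |
| M1 active | FC2/shoulder | active |

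F3/AF8 occurs once active and once sham, so layout does not distinguish them. FC2/shoulder occurs once, always active. Layout therefore identifies 1 of the 3 sessions.

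In a part A model with an intercept, a layout effect L (sensation and expectation tied to the layout worn), a dlPFC effect D and an M1 effect M, the sessions contribute:

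- dlPFC active: intercept + D
- M1 active: intercept + L + M
- sham: intercept

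dlPFC − sham = D, which is estimable. M1 − sham = L + M, and the two cannot be split. The design has rank 3 for 4 parameters.

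**Attribution, across parts**

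Take 8 parameters: intercept, endurance, repeated, active, and the interactions of active with M1, extracephalic, endurance and repeated.

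- Part A plus part B end-of-sequence data: three pairs of columns are identical (endurance and repeated; active×endurance and active×repeated; active×M1 and active×extracephalic). Rank = 8 − 3 = 5.
- Adding part B data after the first session, active and sham: endurance and repeated are no longer identical. Only active×M1 and active×extracephalic remain so. Rank = 8 − 1 = 7.

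Area and montage are thus aliased whichever data are used. Single versus repeated becomes estimable within part B, as (active − sham after the last session) minus (active − sham after the first). Exercise type becomes estimable only because this model has no term for population (parkour practitioners and other jumpers versus sedentary subjects and cyclists) or for timing (before-and-after assessment in part A, stimulation during cycling in part B). Both differ between the parts exactly as exercise type does.

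**Are assessments after the first session planned?** The Abstract, Cognitive tasks and Outcomes sections say so; Outcomes includes average power in the time trial. Study setting and overview and Explosive or endurance task list maximal trials only before and after the sequence and at days 12 and 30. The overview gives the same sequence-level schedule for the common measures, and Neuromuscular assessment also refers to the sequence. These sections do not agree.

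**Sample size, and randomising the sham layout**

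Inputs from Sample size: difference 5.1, SD of paired differences 6.5 (cm assumed), alpha 5% (two-sided assumed), power 90%. For a paired t-test, the noncentrality is (5.1/6.5)·√n on n − 1 degrees of freedom.

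- n = 20: power 91.4%. This is the smallest n reaching 90%, so the stated 20 is reproduced.
- If each subject's one sham were randomised between layouts, about 20/2 = 10 would have a sham matching dlPFC. At n = 10, power is 60%.
- There would be 6 orders × 2 sham layouts = 12 combinations. The layout worn only once would always be active. It falls third in 2 of 6 orders for each sham layout, so in 4 of 12 the third session is knowably active beforehand. In 2 of those 4 it is the dlPFC session.

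**The case against.** The main objective is dlPFC versus sham, and that pair shares a layout and differs only by coded current. A reader might infer that the whole trial is unblinded; the documents do not support this, and the main contrast stands.

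A reader might also infer that all 20 part A subjects will know their M1 session is active. That depends on what they are told. Recruitment and randomisation says that they are informed about the technique and the objectives, but the article does not say whether they learn that there is one sham and which layout it uses. Identification is certain only for someone who sees the electrodes and knows the three conditions.

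A third tempting reading is that the number of sessions is wholly inseparable from exercise type. That is true only at end of sequence. The assessments that several sections plan after the first and after the last session, in active and sham sequences, allow a comparison within part B.

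Finally, the trial is titled exploratory, the Background speaks of seeking understanding, and the analysis section states no test of part A against part B and no decomposition of area and montage. This is fair, and it makes the matter one of wording rather than failed hypotheses. It does not rescue the area and montage aims: no analysis, exploratory or otherwise, can separate two identical contrasts.

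**Conclusion.** The concern holds in a limited form. The Blinding statement claims more than the design delivers: of the three pairwise contrasts in part A, dlPFC versus sham is protected from unmasking by layout, while M1 versus sham and M1 versus dlPFC are not. Area and montage are perfectly aliased, although the Background and the Discussion list both. Exercise type cannot be cleanly separated across parts. Single versus repeated sessions can be addressed within part B for whichever outcomes are really assessed after the first session.

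This rests on Table 1 giving all part A layouts, and on staff who place or see electrodes knowing the three conditions. How often subjects would recognise M1 as active cannot be quantified from the article. The sample size and the main comparison are unaffected; what changes is what the trial may claim about M1, montage and exercise type.

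**What to change.** - **Blinding:** limit the double-blind claim to dlPFC versus sham. State that M1 versus sham and M1 versus dlPFC are not masked by layout, and report them so.
- **Analysis:** keep the main part A comparison to dlPFC versus sham.
- **Background and Discussion:** restate the conclusions as being about two packages (dlPFC-cephalic and M1-extracephalic) and two separate experiments, with no attribution to area as against montage, or to exercise type across parts.
- **Single versus repeated:** restrict this aim to part B, after the first versus after the last session, active versus sham. Reconcile Outcomes with Study setting and overview and with Explosive or endurance task on whether a time trial follows the first session, and check the other measures against the same sections.

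Do not randomise the sham layout. It would leave about 10 of 20 subjects with a matched sham for the main contrast and would expose some dlPFC sessions that are now masked.

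The cost is a wording change and a check of the assessment schedule. No extra subjects or sessions are needed, and the change remains possible although the Trial status section gives recruitment as starting in November 2018.

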#### Study procedure: Part A

In part A, the study will have four phases. The first phase will correspond to the recruitment while other phases will correspond to both inclusion of volunteers and visits for the experimental sessions. The three visits will be organised in the same way and separated by a wash-out of at least 48 h. This period will be necessary to allow a wash-out of the effects of a tDCS session, which persist for several hours [1]. Cognitive and motor tasks and neuromuscular assessments will be realised before and immediately after the stimulation. The detailed procedure is displayed in Fig. 3.

**Fig. 3 Fig3:**
[figure not shown]
Randomised crossover design for COMPETE (part A) (Standard Protocol Items: Recommendations for Interventional Trials (SPIRIT) Figure). *BART* Balloon Analog Risk Task*, BIS-10* Barratt Impulsiveness Scale-10, *dlPFC* dorsolateral prefrontal cortex, *EEfRT* Effort Expenditure for Rewards Task, *M1* primary motor cortex, *MCQ* Monetary Choice Questionnaire, *QIDS-C16* 16-Item Quick Inventory of Depressive Symptomatology, Clinician Rating, *QIDS-SR16* 16-Item Quick Inventory of Depressive Symptomatology, Self-Report

#### Study procedure: Part B

In part B, the study will be comprised of three phases (the detailed procedure is displayed in Fig. 4). The first phase will correspond to recruitment, conducted in the same way as in part A. The second phase will relate to both the inclusion of the volunteers and the period of the first tDCS sequence. Behavioural scores and neuromuscular parameters will be collected at baseline and immediately at the first tDCS session. It will be delivered on a Monday and two daily sessions will be performed during the following days (during the endurance task) up to Friday. Clinical, neuromuscular, and behavioural assessments will be realised once the last tDCS session has been delivered (day 5), and then at day 12 and day 30.

**Fig. 4 Fig4:**
[figure not shown]
Randomised cross-over design for COMPETE (part B) (Standard Protocol Items: Recommendations for Interventional Trials (SPIRIT) Figure). *BART* Balloon Analog Risk Task, *BIS-10* Barratt Impulsiveness Scale-10, *dlPFC* dorsolateral prefrontal cortex, *EEfRT* Effort Expenditure for Rewards Task, *M1* primary motor cortex, *MCQ* Monetary Choice Questionnaire*, QIDS-C16* 16-Item Quick Inventory of Depressive Symptomatology, Clinician Rating*, QIDS-SR16* 16-Item Quick Inventory of Depressive Symptomatology, Self-Report

After the last assessment, crossover will be realised: subjects who underwent sham stimulation sessions will then be submitted to active sessions and vice versa (third phase) with the same design. One month of wash out will be necessary to eliminate the residual effects of the tDCS sequence.

### Sample size

Our sample size calculation is based on the primary efficacy outcome that relates to changes in motor performance before and after a tDCS session during an explosive task (jumps). In a previous study, Lattari et al. [22] showed an 11.2% improvement in the height of the CMJ following a tDCS session, corresponding to a difference of 3.9 cm (Table 1 of Lattari’s et al.). We expect a 15% improvement in our study corresponding to a difference of 5.1 cm. No difference is expected in the sham tDCS group. Considering a significance level of 5%, a power of 90%, and a standard deviation for paired differences of 6.5 (calculated from standard deviations, page 21, Table 1 with an hypothesis of a covariance of measures of 50%), 20 jumpers are included to meet the objectives of the study. Sample size calculation was performed on PASS 13 Power Analysis and Sample Size Software (2014) [39, 40] .

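### The 90% power with 20 jumpers is for a before-after change in one condition; for dlPFC versus sham change it runs from about 65% to 91%, depending on an unstated between-session correlation

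*Protocol article*

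**What the plan says.** The Background section of the protocol article states the aim: "The main objective is to compare the effects of tDCS applied over the left dlPFC with sham tDCS". It describes the design as a "crossover, double-blinded superiority trial comparing active tDCS versus sham tDCS".

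The Sample size section builds the calculation on "changes in motor performance before and after a tDCS session during an explosive task (jumps"). The effect comes from a published before-after result, "an 11.2% improvement in the height of the CMJ following a tDCS session, corresponding to a difference of 3.9 cm", which is raised for this trial: "We expect a 15% improvement in our study corresponding to a difference of 5.1 cm". The remaining inputs are "Considering a significance level of 5%, a power of 90%, and a standard deviation for paired differences of 6.5", where the SD rests on a hypothesised 50% covariance of the measures. Sham appears once: "No difference is expected in the sham tDCS group".

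The section on data management and statistical analyses plans a two-way repeated-measures ANOVA, with condition (three levels) and moment (before, after) as within-subject factors, and Bonferroni correction for multiple testing.

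**The concern.** The trial is sized on one quantity and set up to answer a question about another. Showing that jump height rises after an active session does not show that it rises more than after sham. That needs the active change minus the sham change within each jumper, which is the condition-by-moment interaction for those two conditions.

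A sham change that averages zero still varies from jumper to jumper. Assuming a zero mean leaves the target difference at 5.1 cm, but the sham variability still enters the standard error, and the calculation has no term for it. If the stated 90% is carried over to the active-sham comparison, a null result would be taken as stronger evidence against an effect than the design may be able to give.

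**Working it through.** **Inputs.** From the Sample size section: difference 5.1 cm, SD of paired differences 6.5 cm, 50% covariance of the measures (read here as a correlation of 0.5), alpha 5%, power 90%, n = 20. Assumption: two-sided test, since sidedness is not stated. Power is from the noncentral t distribution.

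**Step 1: reproduce the plan's figure.** For a paired t-test on one set of differences, d = 5.1 / 6.5 = 0.785. The smallest n giving 90% power is 20, and power at n = 20 is 91.4%. The stated sample size is therefore this test, correctly computed.

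**Step 2: SD of the contrast named in the objective.** Let each before-after change have SD 6.5, and let r be the correlation between a jumper's active and sham changes. Then

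SD(active change − sham change) = 6.5 × √(2(1 − r)).

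The expected difference stays at 5.1 − 0 = 5.1 cm.

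**Step 3: power with 20 jumpers.** The last column halves alpha to 0.025, as a Bonferroni correction over two active-sham contrasts would do.

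| r | SD (cm) | Power, alpha 0.05 | n for 90%, alpha 0.05 | Power, alpha 0.025 |
|---|---|---|---|---|
| 0 | 9.19 | 65.3% | 37 | 53.0% |
| 0.25 | 7.96 | 77.6% | 28 | 66.7% |
| 0.5 | 6.50 | 91.4% | 20 | 84.9% |

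**Step 4: where r = 0 comes from.** The covariance of the two changes is

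cov(post_A, post_S) − cov(post_A, pre_S) − cov(pre_A, post_S) + cov(pre_A, pre_S),

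with A for active and S for sham. If every measure in one session has the same covariance with every measure in the other, the four terms cancel and r = 0, whatever the common value. Stable differences in jumping ability therefore do not help this contrast. Applying 50% to all four measures is one such case: Var = 4 × 6.5² × (1 − 0.5) = 84.5, so SD = 9.19. For r near 0.5, about half the variance of a change would have to be shared between a jumper's active and sham sessions.

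**Step 5: a contrast that uses the same data better.** Take the SD per measure as 6.5 (which follows from 6.5 per difference at 50% correlation, if pre and post SDs are equal), and let c be the uniform cross-session correlation. The post-session difference, adjusted for the pre-stimulation difference, has residual variance

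2 × 6.5² × (1 − c) × [1 − ((0.5 − c)/(1 − c))²].

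- c = 0.5: 84.5 × 0.5 × 1 = 42.25, SD 6.50.
- c = 0.3: 84.5 × 0.7 × (1 − 0.286²) = 54.3, SD 7.37.
- c = 0.1: 84.5 × 0.9 × (1 − 0.444²) = 61.0, SD 7.81.

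Simulations that estimate the adjustment from the data give about 90–92% at c = 0.5, 81–83% at c = 0.3 and about 78% at c = 0.1, all before any Bonferroni correction.

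**The case against.** The strongest reply is that the objective does not prescribe a difference of change scores. If the 50% applied across sessions as well, the plain post-session difference between active and sham would also have SD 6.5, and 20 jumpers would give 91.4%. The protocol does not name the interaction as the primary test, and an analysis plan that is not shown may settle this. That stands as a reason not to call the sample size wrong for every active-sham analysis. It does not rescue the text as written: the calculation is described as before versus after a session, its effect is a before-after gain, and the only analysis described has moment as a factor.

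A reader might infer that power is 65% on the plan's own assumptions. The protocol does not support that. It gives 50% for the measures behind one SD and says nothing about correlation between sessions, so 65% needs the added assumption in step 4. The 50% is itself a hypothesis. Keeping 6.5 cm per measure and uniform cross-session correlation, pre-post correlations of 0.6, 0.7 and 0.8 would give interaction power of about 75%, 86% and 96%.

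The title calls the trial exploratory, which softens the consequence. The Background section nevertheless calls it a superiority trial, and the Sample size section claims 90% power to meet the study objectives.

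The 5.1 cm target exceeds the cited 3.9 cm, but both figures are stated openly. That is an optimistic design judgement and no part of this error.

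**Conclusion.** The concern holds in conditional form. The arithmetic behind 20 jumpers is correct, but it answers a single-condition before-after question and gives the sham change no variance. For the difference in change between dlPFC stimulation and sham, the stated 90% is reached only if the two changes correlate at about 0.5. Over r = 0 to 0.5, power is about 65% to 91%; the lower end applies whenever cross-session correlations are uniform. These figures assume a two-sided 5% test, a true difference of 5.1 cm and an SD of 6.5 cm for each change. Bonferroni correction, planned but absent from the calculation, would reduce them.

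It would go too far to conclude that the trial must enrol 37 jumpers. That number belongs to r = 0 with unadjusted change scores, and an adjusted analysis of the same 20 jumpers recovers much of the loss.

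**What to change.** In the Sample size section, name the contrast being powered (dlPFC versus sham). State either the assumed between-session correlation or the SD of the active-minus-sham contrast. Report power for 20 jumpers as a range, about 65–91% for a difference in change at r = 0 to 0.5, and say whether Bonferroni correction applies to that contrast.

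Preferably, make the primary test the dlPFC-minus-sham difference in post-session jump height, adjusted for that session's pre-stimulation value, and quote its power (roughly 78–92% at cross-session correlations of 0.1–0.5, before any Bonferroni correction).

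The cost is one rewritten paragraph and, if the preferred test is adopted, one changed contrast in the analysis. The pre-stimulation values are already collected, so no new data or extra jumpers are needed. The drawback is that the published power becomes less favourable.
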